#### Participants and recruitment

Females presenting to ED within three days of injury with suspected concussion are recruited by ED healthcare professionals. Participants are invited to participate if they are biologically female (self-report), of reproductive age (16–50 years) and have a confirmed diagnosis of concussion from the consulting healthcare professional. The diagnostic criteria for concussion are those outlined in the most recent international consensus statement from the concussion in sport group. [51] Participants will be excluded if they have Polycystic Ovarian Syndrome (PCOS), a pre-diagnosed psychiatric disorder or neurological condition (e.g. epilepsy, cerebral palsy) or if they have had more than three previously diagnosed concussions; these are known modifiers for prolonged recovery. [52, 53] These specific exclusion criteria will be ascertained by the consulting ED healthcare professional as part of the initial routine assessment for concussion. Full inclusion/exclusion criteria are shown in Table 1. The standard concussion assessment is detailed in Fig. 1. Study recruitment commenced February 2022, however there was interruption due to COVID related sickness and changes in the ED through November 2022. The study recommenced in January 2023 and is in progress.

**Table 1 Tab1:** Inclusion and exclusion criteria

Inclusion criteria	Exclusion criteria
Females of reproductive age: 16–50 years (with a menstrual cycle for a minimum of 2 years if naturally cycling)	Had three or more previously diagnosed concussions
Natural regular menstrual cycle 28–35 days long, or Currently taking Oral Contraceptive Pill (OCP), or Currently have Intra Uterine Device (IUD), or	Current concussion was more than 3 days ago
	Post-menopause
	Started taking medication that would alter reproductive hormone concentrations (Corticosteroids, e.g., Prednisone. Antidepressant or Antipsychotic medication) within the last 3 months
	Current clinical diagnosis of an eating disorder
	Pre-diagnosed psychiatric disorder
	Pre-diagnosed neurological condition
	Polycystic Ovarian Syndrome (PCOS)
	Oligomenorrheic (irregular periods), or
	Amenorrheic (loss of periods for 3 months or longer)
Confirmed diagnosis of concussion by a medical doctor (within 3 days of injury)	GCS^a^ score less than 15 at 4 h after initial assessment. These patients may be referred for a CT scan and will not be eligible for the study

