#### Surveys and questions

Survey and question data are collected and managed using REDCap (Research Electronic Data Capture) which is a secure, web-based software platform designed to support data capture for research studies. [56, 57] Participants are provided with an online link to REDCap via email. A new link is sent every seven days after initial appointment until a full return to work/study is reported. It takes approximately 10 min to complete all questions each week.

Two concussion specific questions are asked only once, seven days after the initial appointment. The first question relates to concussion history and is utilised to capture the number of previous concussions the participant has had. This information is important as prior concussion can impact recovery from subsequent concussions. [52] The second question is used to capture whether the participant’s concussion is sport related or not.

Participants are also asked to complete the Low Energy Availability in Females Questionnaire (LEAF–Q) online seven days after initial assessment and then at seven-day time intervals throughout recovery. The LEAF-Q [58] is designed and validated to evaluate physiological symptoms of insufficient energy intake or low energy availability (LEA). The LEAF-Q contains questions regarding injuries, gastrointestinal and reproductive function. In Sect. 3.2 three questions (19 items) relate to menstrual function including recent menstrual history. This questionnaire section is used to determine hormonal profile of participants and has been modified as outlined below.

Part C of Sect. 3.2 includes the following question:C: Do you have normal menstruation? Yes ☐ No (go to question C6) I don’t know (go to question C6)C1: If yes, when was your last period? 0–4 weeks ago ☐ 1–2 months ago ☐ 3–4 months ago ☐ 5 months ago or more ☐

This question has been modified to capture more accurate detail about the last menstrual cycle as follows:C: Do you have normal menstruation? Yes ☐ No (go to question C6) I don’t know (go to question C6)C1: If yes, when was your last period? 1 week ago ☐ 2 weeks ago ☐ 3 weeks ago ☐ 4 weeks ago ☐ 1–2 months ago ☐ 3–4 months ago ☐ 5 months ago or more

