Participants are categorised into one of five hormone profiles as follows; 1) Follicular phase if question C1 is answered as “1 week ago”, 2) Mid-cycle if question C1 is answered “2 weeks ago”, 3) Luteal phase if question C1 is answered “3 weeks ago” or “4 weeks ago”, 4) Oligomenorrheic if C1 was answered “1–2 months ago”, “3–4 months ago” or “5 months ago or more”, 5) Using contraceptive if question 3.1a is answered “yes”.

Scoring of question 3.2 remains the same, i.e., if a participant ticks any of the boxes within the 0–4 weeks’ timeframe the same score is applied as the original question. In eumenorrheic participants this will help estimate menstrual cycle phase at point of injury. This information is used to understand any association between hormonal profile and or LEAF_Q score with symptom severity and duration of concussion.

The Brain Injury Screening Tool (BIST) is a brief screening tool for use on initial presentation after injury to guide health care pathway decision making and to monitor symptoms and recovery over time. [59] The BIST was developed in the NZ context to fit the clinical environment and to provide consistency across multiple environments and referral pathways (e.g. GP clinic, ED, Urgent Care Centres), the tool has also been psychometrically tested. There are two sections in the BIST; the first section is used to determine if there are any clinical ‘red flags’ which require referral to hospital, therefore this component is not included in this study. The second section of the BIST includes a 16-item symptom report scale for patients to rate how much they now experience the symptoms listed on a scale of 0 (not at all) to 10 (severe). Higher symptom scores are indicative of higher symptom burden. Participants are asked to complete this part of the BIST at point of presentation with injury and at seven-day time intervals throughout the study to monitor symptoms and recovery over time.

The final question asks if the participant has made a full return to work/study and how many follow-up appointments they had. The number of days between injury and full return to work/study will be used as a proxy for recovery. This question is included in the weblink sent at all timepoints (i.e., 7, 14, 21, 28 days etc.) until the participant reports they have achieved a full return to work/study, at which point participation in the study will be complete. Detail of information collected each week is included in Table 2.

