## Data analysis

In this study a range of statistical tests will be used to analyse the data corresponding to the four aims. Aim 1 will use Cox proportional hazards regression to determine if the time to recovery from concussion (measured in days), differs among groups categorised by hormone profile at the point of injury (five profiles: Follicular phase, Midcycle, Luteal phase, oral contraception, IUD). Aim 2 will apply an ANOVA to compare the ratios of miR-27a-5p/miR-30a-3p expression, across these five groups. Model-estimated means and pairwise contrasts between groups will also be computed. For Aim 3, the focus is on whether self-reported symptoms, quantified both as the number of symptoms present (range 0–16) and as a total symptom burden (sum of severity scores; range 0–160), differ among hormone profile categories. These dependent variables will be analysed using ANOVA, with the five hormone profiles specified as the independent variable. Aim 4 will employ a linear mixed model to investigate changes in low energy availability across the recovery period. This model will incorporate the day of recovery and total symptom burden as fixed effects and will account for repeated measures over time by specifying participant as a random effect. The interaction between symptom burden and recovery time will also be evaluated to understand if these variables are collectively associated with low energy availability.

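### The item that assigns cycle phase is skipped by eligible, naturally cycling women who do not answer Yes to normal menstruation, so they have no hormone profile for Aims 1–3

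*Protocol article*

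**What the plan says.** All of the following is in the Protocol article.

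- **Purpose of the items.** Surveys and questions says of the menstrual part of the LEAF-Q: "This questionnaire section is used to determine hormonal profile of participants".
- **Gate.** Item C is printed before and after modification, and the routing is the same in both: "Do you have normal menstruation? Yes ☐ No (go to question C6) I don’t know (go to question C6". The follow-on item is conditional: "C1: If yes, when was your last period? 1 week ago", with further answer boxes after it. Only the boxes of C1 were changed.
- **Classification.** "Participants are categorised into one of five hormone profiles as follows". Follicular, mid-cycle and luteal are each defined by an answer to C1. So is the fourth: "4) Oligomenorrheic if C1 was answered “1–2 months ago”, “3–4 months ago” or “5 months ago or more". The fifth uses a different item: "5) Using contraceptive if question 3.1a is answered “yes". Neither C itself nor C6 and the items after it have a role.
- **Eligibility.** Table 1 admits "Natural regular menstrual cycle 28–35 days long, or Currently taking Oral Contraceptive Pill (OCP), or Currently have Intra Uterine Device (IUD), or" and excludes oligomenorrheic and amenorrheic women.
- **Use.** Data analysis tests whether time to recovery "differs among groups categorised by hormone profile at the point of injury", and Aims 2 and 3 use the same grouping. The five groups named there are three cycle phases, oral contraception and IUD.

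**The concern.** The boxes of C1 were refined so that cycle phase could be read from them, but the routing that hides C1 from some respondents was kept. Hormone profile is the grouping variable in Aims 1, 2 and 3. A woman without a profile cannot enter any of those analyses, even though her saliva sample, BIST scores and return-to-work date are in hand.

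The loss would also be selective. It can remove only women who do not use contraception, and among them those who are unsure of their cycle or do not regard it as normal. With about six evaluable women per group, a few losses confined to the three cycle-phase groups would thin exactly the comparisons that the study is about.

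**Working it through.** **1. Tracing the printed rules**

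| Answer at C | Item 3.1a (contraceptive) | C1 asked? | Profile |
|---|---|---|---|
| Yes | no | yes | one of profiles 1–4, from C1 |
| No or I don't know | yes | no | profile 5, from 3.1a |
| No or I don't know | no | no | none |

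The gap is the third row. The rule sets out to place participants in one of five profiles, and no profile covers this row.

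**2. Can an eligible woman be in the third row?** Table 1 screens for a regular natural cycle of 28–35 days. Item C asks about *normal* menstruation, and the item as printed does not define the word. A woman with a regular cycle may be unsure whether her periods count as normal, and *I don't know* is an offered answer. Screening should make *No* uncommon among non-users of contraception, but it does not prevent *I don't know*.

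**3. Reproducing the planned sample size.** Inputs from Sample size calculation: log hazard ratio 0.4055, covariate SD 1.5, R² 0.2, event rate 0.9, power 80%, type I error 0.05 (taken as two-sided, which reproduces the figure; one-sided gives 24).

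- Events = (1.960 + 0.842)² / [1.5² × 0.4055² × (1 − 0.2)] = 26.52
- N = 26.52 / 0.9 = 29.47, rounded up to 30, as stated
- With 20% drop-out: 30 / 0.8 = 37.5, rounded up to 38, as stated

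**4. Size of the loss, under assumptions.** The protocol gives neither the share of women who cycle naturally nor the share of those who would not answer Yes. I assume:

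- 60% cycle naturally (three of the five analysis groups, equally filled), so 0.6 × 30 = 18 evaluable women;
- 5%, 10% or 20% of those 18 are lost at the gate.

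Power = Φ(√(n × 0.9 × 0.8) × 1.5 × 0.4055 − 1.96)

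| Lost at gate | Women lost | n analysed | Power |
|---|---|---|---|
| 0% | 0 | 30 | 0.807 |
| 5% of 18 | 0.9 | 29.1 | 0.795 |
| 10% of 18 | 1.8 | 28.2 | 0.782 |
| 20% of 18 | 3.6 | 26.4 | 0.755 |

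At the 20% end, the three cycle-phase groups go from 18 / 3 = 6 to 14.4 / 3 = 4.8 women each, while the contraceptive groups lose none.

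The 60% matters. In the extreme case that all 30 evaluable women cycled naturally, the same 5–20% would remove 1.5–6 women and power would be 0.787–0.715.

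The formula treats exposure as one covariate, whereas the analysis has five groups. These power figures are therefore only a rough guide to the effect of losses concentrated in three of the groups.

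**The case against.** **The gap is small and its size is unknown.** This stands. Table 1 should remove most non-users who would answer *No*, and nothing in the protocol indicates how many regular cyclers would answer *I don't know*. At the low end of the assumed range the loss of power is negligible. The stronger reason to act is that the loss is selective and avoidable.

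**The gate may be deliberate.** The section limits phase estimation to eumenorrheic participants, and the limitations section warns that cycle recall is inaccurate. Declining to assign a phase to a woman who doubts that her periods are normal is defensible, and asking her C1 exchanges missing exposure for possible misclassification. This stands as a cost of the fix and is met by a flag and a sensitivity analysis. It does not explain why a woman already accepted as having a regular cycle should be left without any category.

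**The live form may differ, and unclassified responses may be handled elsewhere.** The REDCap branching, C6 and any analysis plan are not shown. But the article prints both the routing and the classification rule, and those two do not fit together. The LEAF-Q is repeated weekly, so a later Yes is possible, yet no rule is given for using it.

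**Stronger readings that the protocol does not support.**
- A reader might infer that every woman answering *No* or *I don't know* is unclassified. Contraceptive users among them are placed by item 3.1a.
- A reader might also make much of the fact that the oligomenorrheic class can be reached only by women who have just called their menstruation normal. That follows from the routing, but Table 1 excludes such women, Data analysis has no such group, and no passage gives the class the task of catching screening failures. The mismatch between the class, Table 1 and the group list is a separate matter that the skip neither causes nor cures.
- Applying the same shares to the 38 recruited gives 1.1–4.6 women, but that count is before drop-out and cannot be set against the 30 evaluable.

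**Conclusion.** The point holds in a limited form. As printed, the questionnaire withholds the only item that assigns cycle phase from women who met the regular-cycle criterion, use no contraception, and answer *I don't know* or *No* at C. They have no value on the exposure of Aims 1–3. Aim 4, whose model does not use hormone profile, does not depend on this.

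Under the assumed shares, 0.9–3.6 of 30 evaluable women are lost, all from the naturally cycling groups, and power on the protocol's formula falls from about 81% to 80–76%. Both the 60% and the 5–20% are assumptions; the protocol supports neither. The conclusion about the routing rests on the printed text alone and does not depend on them.

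**What to change.** 1. Show C1 to every woman not classed as a contraceptive user, whatever she answers at C.
2. Count C1 towards the LEAF-Q only when C is answered Yes, so that scoring stays as it is.
3. Assign phase from C1 for all women who met the Table 1 cycle criterion.
4. Flag those who answered *No* or *I don't know* and repeat the Aim 1–3 analyses without them, because their phase may be less certain.
5. Ask C1 of any enrolled woman who skipped it. The article counts 14 who had started by 18 August 2023. Answers obtained late rest on longer recall and should carry the same flag.
6. Separately, reconcile the oligomenorrheic profile with the Table 1 exclusion and with the group list in Data analysis.

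The cost is one change to the form's branching, a sentence in the classification rule, one sensitivity analysis and a short follow-up question for a few women. The downside is some possible misclassification of phase, which the flag makes visible.

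### The modified LEAF-Q item C1 fixes neither first nor last day of bleeding and has no box for a current period, so women on the same cycle day can receive different hormone profiles

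*Protocol article*

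**What the plan says.** All of this is in the Protocol article, section Surveys and questions, unless stated otherwise.

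- The original item had a single box for the most recent weeks: "when was your last period? 0–4 weeks ago ☐ 1–2 months ago".
- The reason given for the change: "This question has been modified to capture more accurate detail about the last menstrual cycle as follows". The new boxes are: "when was your last period? 1 week ago ☐ 2 weeks ago ☐ 3 weeks ago ☐ 4 weeks ago", followed by boxes in months.
- The answer is turned into a phase: "Follicular phase if question C1 is answered as “1 week ago"; "Mid-cycle if question C1 is answered “2 weeks ago"; "Luteal phase if question C1 is answered “3 weeks ago” or “4 weeks ago". Any box in months gives the profile oligomenorrheic.
- On scoring: "if a participant ticks any of the boxes within the 0–4 weeks’ timeframe the same score is applied" as before.
- The LEAF-Q is first completed seven days after the initial assessment (also Table 2). Women present within three days of injury.
- Data analysis compares five groups: follicular, mid-cycle, luteal, oral contraception and IUD. They are used in the Cox model for Aim 1 and in the ANOVAs for Aims 2 and 3. Table 1 lists oligomenorrhea as an exclusion.

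**The concern.** With one box for 0–4 weeks, it hardly mattered which day of the period a woman counted from. Once that box is split into single weeks that decide the phase, a difference of a few days moves her to another group. The stem still asks only about the last period. It names no day and no rounding rule, and the boxes now start at one week.

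This is separate from recall error. A woman who remembers every date exactly still has two defensible answers. Phase defines three of the five groups in Aims 1 to 3, including the primary aim. The study plans 30 evaluable and 38 recruited women, so a few women in the wrong group could change a comparison.

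**Working it through.** The plan gives no figure for classification error, and its sample size is not in question here.

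**Inputs.** Boxes and phase rule: Surveys and questions. Cycle length L = 28–35 days: Table 1. Assumed, because the documents do not give them: bleeding length B of 3, 5 or 7 days, a random cycle day, answers to the nearest week (minimum one), and anything past the 4-week box ticked as 1–2 months.

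**Step 1: examples.**
- Bleeding began 12 days ago and ended 7 days ago. From the first day: 12/7 = 1.7, so 2 weeks, mid-cycle. From the last day: 7/7 = 1 week, follicular.
- Cycle day 21, 5 days of bleeding. From the first day: 20/7 = 2.9, so 3 weeks, luteal. From the last day: 16/7 = 2.3, so 2 weeks, mid-cycle.

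**Step 2: how often the readings conflict.** The phase changes when the count passes 10.5, 17.5 or 31.5 days. (The boundary at 24.5 separates 3 from 4 weeks, both luteal.) Counting from the last day lowers the count by B, so the readings disagree for B days after each boundary:

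share = [2B + max(0, min(B, L − 31.5))] / L

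| | B = 3 | B = 5 | B = 7 |
|---|---|---|---|
| L = 28 | 6/28 = 21% | 10/28 = 36% | 14/28 = 50% |
| L = 35 | 9/35 = 26% | 13.5/35 = 39% | 17.5/35 = 50% |
| Simulated, L spread over 28–35 | about 22% | about 35% | about 48% |

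Here women now bleeding tick 1 week under both readings. A stricter count uses whole days, with the two counts B − 1 days apart and only days after bleeding included. It gives 4, 8 or 12 of 28 days (14%, 29%, 43%), and 11–51% of a 35-day cycle depending on rounding.

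These shares contrast all women reading one way with all reading the other. If half read it each way, two women on the same cycle day disagree in 2 × 0.5 × 0.5 × 35% = about 17% of pairs. If all read it alike, none do.

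**Step 3: women bleeding when asked.** At the mid-range cycle of 31.5 days these are 3/31.5, 5/31.5 or 7/31.5, about 10%, 16% or 22%. Take a woman whose period began 2 days ago and who gives the start of the previous one.
- 28-day cycle: 30/7 = 4.3, so 4 weeks, luteal.
- 35-day cycle: 37/7 = 5.3, past the 4-week box, oligomenorrheic.

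With L over 28–35 and 5 days of bleeding, the count L + D (D = days since this period began, 0–5) stays below 31.5 in an area of 3.5²/2 = 6.125 out of 7 × 5 = 35. So about 1 − 6.125/35 = 82% fall past 4 weeks; simulation gives 78–81%. If she gives the last day of the previous period, the count is L + D − 5. It exceeds 31.5 in only 6.125/35, about one in six, so she is mostly luteal.

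**Step 4: the survey lag.** The first answer comes 7 to 7 + 3 = 10 days after injury. Take phase at injury as the same rule applied to days since the first day of bleeding at injury, with late days of long cycles counted as luteal. With B = 5, boxes counted from the first day to the survey day match it for about 30% of women at a 7-day lag, and boxes counted from the last day for about 65%. At 10 days it is 11% and 36%. Counting from the last day takes off about 5 days, which partly cancels the lag. In addition, 7/31.5 = 22% to 10/31.5 = 32% of women start a new period between injury and survey.

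**The case against.** **Meaning of the first box.** The scoring sentence refers to a 0–4 weeks' timeframe, so 1 week may have been meant as 0–1 week. That sentence concerns the LEAF-Q score, is not part of the item, and leaves the counting day open. The 22–48% already assumes that women now bleeding tick 1 week.

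**Already conceded.** Strengths and limitations admits self-reported profiles, no gold-standard verification and recall error. It does not mention an item with two valid answers.

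**Survey timing.** This objection stands in large part. Because the LEAF-Q is answered 7–10 days after injury, a conflict between readings is not the same as an error in phase at injury. A woman bleeding at the survey may well have been late in her previous cycle when injured, so luteal can be the right label. In the 12-day example with a 7-day lag, she was 12 − 7 = 5 days from onset at injury, and the follicular answer fits better than mid-cycle. Adding a first-day anchor and a current-period box while still counting to the survey day would not help.

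**Stronger readings.** A reader might infer that 22–48% of women will be misclassified. The documents give no mix of readings, bleeding length or rounding, so they do not support that. A reader might also infer that group differences are pulled towards zero. With several categories, misclassification need not weaken every contrast, and nothing in the documents fixes its direction.

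**Conclusion.** The point holds as a defect in how the exposure is measured. The printed item and the printed rule together allow two profiles for the same cycle day. The article states both in full, so this is not detail left to a longer protocol.

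The rule can split women on the same cycle day; it does not do so on every day or for every pair. The size is at most about 22–48% of naturally cycling women over the possible mixes of reading, under the assumptions above, and the true share is unknown.

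Some women with regular cycles who are bleeding when asked can be labelled oligomenorrheic. Table 1 excludes that category, Data analysis has no group for it, and the article does not say what would happen to them. This is the more common result if they give the start of the previous period; if they give its last day, luteal is. The effect on the estimates for Aims 1 to 3 has no established direction.

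**What to change.** For phase, replace the C1 boxes with a request for the calendar date of the first day of the most recent period that began on or before the injury date, and ask whether another has begun since. Compute the days from that date to the injury date. Assign phase from that count with day ranges written down in advance, covering cycles up to 35 days. Do not count to the survey day, and do not simply add a current-period box to the existing list.

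For LEAF-Q scoring, keep the original C1 boxes, or derive them from the date of the most recent period, so that the score is unchanged.

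The cost is one or two REDCap fields. Women already enrolled (14 had started by 18 August 2023) can be asked once. The small downside is that some dates will be approximate, the more so for women asked long after injury.

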Sex differences are evident in concussion. [5–14] Females often have more severe symptoms that are longer in duration. [15–18] Studies in female athletes also show that symptom endorsement at baseline (i.e., when there is no injury) is more prevalent than that seen in males. [19] Underlying mechanisms for these observed sex differences are not yet well understood and sex as a biological variable in injury recovery remains understudied. [20] Limited data show that sex differences in concussion outcomes (i.e., severity and duration of symptoms) first appear during adolescence, are evident throughout the reproductive years, but that postmenopausal women have similar or better outcomes than men. [5] Women have a considerable physiologic change when transitioning between these life stages with altered levels of estrogen and progesterone. Bi-directional relationships between female sex hormones and concussion could influence symptoms and recovery outcomes. [4, 5, 21, 22] Primary female sex hormones, estrogen and progesterone are typically associated with reproduction, but these hormones are powerful biochemical messengers that influence every body system including, temperature regulation, macronutrient metabolism, hydration, central nervous system fatigue, and brain bioenergetics. [23–26] During reproductive years, estrogen and progesterone fluctuate across the menstrual cycle, which typically lasts 21–35 days. [27, 28] Hormone related symptoms have significant overlap with those symptoms associated with concussion and are similarly considered across physical, cognitive, emotional and sleep related domains. Low Energy Availability (LEA) occurs when dietary energy intake is insufficient to support energy expended in exercise and results in inadequate energy to support the functions required by the body to maintain optimal health; prolonged LEA is a clinical concern that disproportionately affects females, can disrupt endocrine function [29, 30] and presents with a similar set of symptoms to concussion. The prevalence of LEA ranges from 33.5% in recreationally active (tier 2 [31]) females [32] to 59% in sub-elite [33] (tier 3 [31]) and 88% in professional female football players [34] and could be a potential modifier in concussion. Female specific research is therefore needed to understand how sex hormones interact with concussion and to what extent concussion may impact hormone regulation and symptoms.

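### Cycle phase is assigned from weeks since last period with no use of cycle length, although eligible cycles span 28 to 35 days, so the rule itself puts some naturally cycling women in the wrong phase or in an excluded category

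*Protocol article*

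**What the plan says.** Table 1 (Participants and recruitment) admits a naturally cycling woman only with a "Natural regular menstrual cycle 28–35 days long", and lists as an exclusion "Oligomenorrheic (irregular periods), or" amenorrhoeic.

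Under Surveys and questions, the modified LEAF-Q item C1 asks when the last period was and offers boxes for 1, 2, 3 and 4 weeks, then 1–2 months and longer. The hormone profile follows from the ticked box:

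- "Follicular phase if question C1 is answered as “1 week ago"
- "Mid-cycle if question C1 is answered “2 weeks ago"
- "Luteal phase if question C1 is answered “3 weeks ago” or “4 weeks ago"
- "Oligomenorrheic if C1 was answered “1–2 months ago”, “3–4 months ago” or “5 months ago or more"

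A fifth profile covers contraceptive users and comes from a different question. The same section says that C1 is meant to help estimate phase at the time of injury. No step uses the woman's own cycle length, although the Background acknowledges that the hormones "fluctuate across the menstrual cycle, which typically lasts 21–35 days". The Data analysis section compares follicular, mid-cycle, luteal, oral contraception and IUD groups; it has no oligomenorrhoeic group.

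**The concern.** Each of the first two phase boxes is one week wide, and the eligible cycle lengths also differ by up to one week. If the luteal phase is roughly constant, a longer cycle mostly means later ovulation, so the same answer to C1 means different phases in a 28-day and a 35-day woman. At the late end, a regular 35-day woman can be more than four weeks past her last period and still be within a normal cycle.

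Hormone profile at injury is the exposure in Aims 1, 2 and 3, and 38 women are to be recruited across five analysis groups, so a few misplaced women can change a group noticeably. An eligible woman labelled oligomenorrhoeic carries a status that Table 1 excludes and has no place in the planned comparison. This error comes from the rule, so perfect recall and exact back-dating to the injury would not remove it.

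**Working it through.** The article gives no misclassification figure to reproduce. Its sample size (30, or 38 with dropout) is not in dispute and does not enter here.

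**From the article:** eligible length L = 28 to 35 days; box 1 = follicular, 2 = mid-cycle, 3 or 4 = luteal, longer = oligomenorrhoeic.

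**Assumed, because the article does not say:** luteal phase 14 days, so ovulation on cycle day L − 14; mid-cycle = ovulation ±2 days; injury equally likely on any cycle day; the eight lengths equally common; phase judged on the injury day. Elapsed days d run from 0 (first day of bleeding) to L − 1. Ovulation then falls at d = L − 15 and mid-cycle covers d = L − 17 to L − 13. Answers below one week are taken as '1 week ago'.

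**Days covered by each label under three ways of answering in weeks:**

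| Reading | Follicular | Mid-cycle | Luteal | Oligomenorrhoeic |
|---|---|---|---|---|
| Nearest week | 0–10 | 11–17 | 18–31 | 32+ |
| Rounded up | 0–7 | 8–14 | 15–28 | 29+ |
| Rounded down | 0–13 | 14–20 | 21–34 | 35+ |

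**A 35-day cycle** (follicular d 0–17, mid-cycle 18–22, luteal 23–34):

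- Nearest: 7 follicular days labelled mid-cycle (11–17), 5 mid-cycle days labelled luteal (18–22), 3 luteal days labelled oligomenorrhoeic (32–34). Total 15/35 = 43%; oligomenorrhoeic 3/35 = 9%.
- Up: 7 follicular labelled mid-cycle (8–14), 3 follicular labelled luteal (15–17), 5 mid-cycle labelled luteal, 6 luteal labelled oligomenorrhoeic (29–34). Total 21/35 = 60%; oligomenorrhoeic 6/35 = 17%.
- Down: 4 follicular labelled mid-cycle (14–17), 2 mid-cycle labelled luteal (21–22). Total 6/35 = 17%; oligomenorrhoeic 0.

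If a woman keeps ticking '4 weeks ago' until cycle day 30 or 31, the oligomenorrhoeic share is (35 − 30)/35 = 14% or (35 − 31)/35 = 11%, inside the 9% to 17% range.

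**Wrongly labelled days at each length:**

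| L | 28 | 29 | 30 | 31 | 32 | 33 | 34 | 35 | Mean of days/L |
|---|---|---|---|---|---|---|---|---|---|
| Nearest | 2 | 2 | 2 | 4 | 6 | 9 | 12 | 15 | 20% |
| Up | 4 | 6 | 9 | 12 | 15 | 17 | 19 | 21 | 40% |
| Down | 8 | 6 | 4 | 2 | 2 | 2 | 4 | 6 | 14% |

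The oligomenorrhoeic label first appears at L = 33 (nearest) or L = 30 (up), and never when answers are rounded down.

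**Sensitivity of the overall mean:** a ±3-day window gives 19%, 41% and 13%. Ovulation one day later gives 24%, 45% and 13%. Varying luteal length over 12 to 16 days, the window over ±2 to ±3 days and the ovulation day by one gives about 13% to 56% across the three readings.

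**The case against.** The article presents C1 only as a help in estimating phase, and Strengths and limitations of the study concedes self-report, recall error and no gold-standard verification. That is fair, but those caveats concern faulty answers, whereas the error here arises from correct ones.

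The size does depend on how women answer and on physiology that the article does not state. C1 also does not say whether the count starts at the first or last day of bleeding. Counting from the end would lower the weeks reported and move some late-cycle days back into the luteal box; this variant was not enumerated.

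Four stronger readings are tempting and are not supported:

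- A reader might infer that the cut-offs suit a 28-day cycle and simply worsen with length. Under rounding down it is the other way round at the ends: 8/28 = 29% wrong at 28 days against 17% at 35.
- A reader might infer that the mid-cycle group would consist mostly of follicular-phase women. This holds for long cycles if answers are to the nearest week or rounded up. Under rounding down, the truly mid-cycle days among those so labelled are 2 + 3 + 4 + 5 + 5 + 5 + 4 + 3 = 31 of 56 (55%) over lengths 28 to 35.
- A reader might infer that every contrast is pulled towards zero. With several exposure categories, some pairwise contrasts can move away from the null.
- A reader might infer that usual cycle length is already on file from screening. The criterion presupposes some knowledge of it, but the article does not say that a length in days is recorded. It may be among LEAF-Q items that are not reproduced.

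Two neighbouring matters are separate and not counted here: the differing lists of five profiles in Surveys and questions and in Data analysis, and the first administration of C1 seven days after assessment.

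**Conclusion.** The concern stands in conditional form. The printed classification rule ignores cycle length and does not fit the printed eligibility range. The excluded label reaches about 9% to 17% of days in a 35-day cycle if answers are to the nearest week or rounded up, and no eligible day if they are rounded down. Averaged over eligible lengths, some wrong-phase assignment remains under every reading tried: about 14% to 40% under the base assumptions, and about 13% to 56% when these are varied.

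The percentages are of cycle days in women not using contraception, not of all participants; the article gives neither the share of such women nor their distribution of cycle lengths. The consequence is a blurred exposure in Aims 1 to 3. Attenuation is the likely direction but is not assured for each pairwise contrast.

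**What to change.** Reconcile Table 1, the classification rule in Surveys and questions, and the groups in Data analysis. Replace the week boxes, for the purpose of classification, with two fields: the date of the first day of the last period and the usual cycle length. Derive phase on the injury date by counting back from the expected next period (last period plus usual length), with the mid-cycle and luteal windows stated in advance. Do not classify a woman with a stated regular cycle of up to 35 days as oligomenorrhoeic only because her answer exceeds '4 weeks ago'. The original LEAF-Q scoring can be kept by mapping the date back to its categories.

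The cost is two survey fields and a changed derivation rule, with no extra visit or assay. Women already enrolled (14 had started by 18 August 2023) would need to be asked if the information was not recorded. Dates and usual length remain subject to recall error, so the stated limitation stays.
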